### Participants

Participants were recruited from elderly people, aged between 60 and 75 years old, referred to the audiology clinics of Iran University of Medical Sciences and were informed by phone about the study. They were selected based on previous clinical examination, including otoscopy, tympanometry and pure tone audiometry test (PTA) to identify type and level of a hearing loss. In a preliminary interview, speech perception difficulty was evaluated with a question if they had difficulty in understanding speech in noise. Those who respond yes were entered into the study. Later to define difficulty in understanding speech in noise we adapted questionnaire which was used by Tokgoz-Yilmaz
*et al*.
^25^.

We performed Mini Mental State Examination (MMSE) questionnaire in order to rule out prominent cognition difficulty in participants.

Participants were informed that can withdraw from the study at any time. Privacy concerning information and results of participants are respected.

The schematic diagram of study procedures is shown below
*Extended data:* Figure S1.

***Inclusion and exclusion criteria***.
*Inclusion criteria:* individuals with mild to moderate hearing loss and aged between 60–75 years, having diploma or higher degree; right-handedness (assessed using Edinburgh handedness inventory); speaking native language and being monolingual; complaint about speech in noise perception difficulties and normal condition of middle ear function.

*Exclusion criteria:* those who do not meet the inclusion criteria, unwillingness for participation in each step of study, conductive hearing loss and abnormal middle ear, central nervous system disease, head trauma, history of seizure attack and epilepsy, and use of psychiatric and nervous system drugs. Individuals with obvious cognitive problems, as diagnosed by Mini Mental State Examination (MMSE), were also excluded.

***Sample size***. The following formula is used to determine the number of samples in each group with the concern that the two groups are independent and dependent variables in this study are quantitative.
$$\text{n}=\frac{{\left(Z_{1-\frac{\text{α}}{2}}+Z_{1-\text{β}}\right)}^{2}({\sigma_{1}}^{2}+{\sigma_{2}}^{2})}{{\left({\text{μ}}_{1}-{\text{μ}}_{2}\right)}^{2}}$$

α1: standard deviation of the studied variable in the first group (case, exposed, or intervened)

α2: standard deviation of the studied variable in the second group (control, unexposed, or compared)

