μ1: mean of the studied variable in the first group

μ2: mean of the studied variable in the second group

α=0.05

β=80%

Z= 1.96

Based on previous studies, a power of 85% and level of significance of 95% was determined for this study. We obtained a sample size of 15 individuals for each group (total = 30), which takes into consideration a 20% drop out.

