### Study design

The study will not involve complications for participants, but if there is extreme difficulty with cooperation for participants the test will be discontinued. All participants were informed both orally and in writing about the study process. Written consent to participant were obtained before the study start. There is no criteria for intervention modification in this study protocol. To improve adherence to intervention protocols, every training session the examiner provide feedback to all participants and inform them about the training progress. The rehabilitation sessions and duration are flexible for participant.

We randomly assigned participants in 1:1 ratio, intervention and control group. The intervention group undergo the rehabilitation training program.

The two groups were matched for age and gender. Those in the control group do not receive any rehabilitation programs during the study. The randomization was applied by random number table (those assigned an odd number, control group; those assigned an even number, intervention group).

***Study procedures***. Pre-rehabilitation, the SNR (50%) of all participants was measured using the word in noise (WIN) test. In addition, a binaural TFS test and the SSQ questionnaire score of all participants are evaluated (see section
*Outcomes* below).

***Rehabilitation training***. Participants identify the set of 16 consonants using one-interval forced-choice procedure and feedback with correct answer. On each test the participants select one of the stimuli from the set of 16 syllables. The participants are informed while the stimulus is presented that they should identify its middle consonant. Following each stimulus presentation, a 4 × 4 visual display of the response alternatives appear on a computer monitor and the participant select the response by using the computer mouse.

Each participant select a box, if they click the box correctly, the box turn green and if they choose the wrong answer, the box turn red. The participant is given visual feedback by showing the correct VCV with a yellow box. No time limit is be imposed on the participant's responses. Each experimental run consists of 64 trials derived from a different random-order presentation of the 64 syllables in the stimulus set. Each run is last 16 to 30 min depending on the participant's response time. The total duration of rehabilitation sessions are e five weeks. Experiments are controlled by a desktop PC.

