## Study status

The enrolment of the patients has been performed and the allocation will be performed in the near future. The study started in November 2019 and will continue until December 2020.

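### Odd/even assignment from a number table is simple randomisation: as written it does not deliver the stated age-and-gender matching or secure 15 per arm

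*Protocol article*

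**What the plan says.** The Study design section makes three statements about allocation:

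- Ratio: "We randomly assigned participants in 1:1 ratio, intervention and control group".
- Balance: "The two groups were matched for age and gender".
- Mechanism: "The randomization was applied by random number table (those assigned an odd number, control group; those assigned an even number, intervention group".

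The sample-size paragraph under Participants sets the arm sizes: "We obtained a sample size of 15 individuals for each group (total = 30), which takes into consideration a 20% drop out". On timing, the Study status section says: "The enrolment of the patients has been performed and the allocation will be performed in the near future". The article mentions no pairing, stratification, blocking or minimisation.

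**The concern.** A number read from a table for each person, with its parity deciding the arm, is a fair coin toss per person. It carries no information about age or gender and does not stop when an arm reaches 15. So the stated mechanism, followed exactly, does not produce the matching stated next to it and does not fix the planned arm sizes.

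Two things are at stake. The first is balance: 30 people is few enough for chance differences in age or gender to be sizeable. The second is integrity. Someone told both to use odd/even numbers and to end with matched groups has no written procedure for doing so. One way to get there is to choose or move people after their numbers are known, which undermines the random comparison and cannot be repaired in the analysis. The timing conflict adds to this, because groups that have not yet been formed cannot already be matched.

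**Working it through.** **Inputs from the protocol article.** 30 participants, 15 planned per arm, after allowing for 20% dropout (Participants, sample size); 1:1 ratio and odd/even rule (Study design); eligible ages 60 to 75 (Participants); two-sided 5% level and 85% power (sample-size text, although the input list beside it shows 80% against β).

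**The plan's own figure.** The 15 per group cannot be reproduced, because no means or standard deviations are given. It is consistent with 12 evaluable per group: 12 / (1 − 0.20) = 15.

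**Arm sizes.** Under the odd/even rule the number X in the intervention arm is Binomial(30, 0.5).

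- P(X = 15) = C(30,15) / 2^30 = 155,117,520 / 1,073,741,824 = 0.144, so the arms are unequal in 85.6% of runs.
- P(18:12 or worse) = 2 × P(X ≤ 12) = 0.362.
- P(20:10 or worse) = 2 × P(X ≤ 10) = 0.099.

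**Gender.** The article gives no gender mix. Assume 15 men among 30 and, generously, that 15:15 is forced. The number of men a in one arm is then hypergeometric.

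- P(a = 7 or 8) = 2 × C(15,7) × C(15,8) / C(30,15) = 2 × 6,435² / 155,117,520 = 0.534. These splits differ by one man.
- P(arms differ by 3 or more men) = 1 − 0.534 = 0.466.
- P(a = 6 or 9) = 2 × 5,005² / 155,117,520 = 0.323, so P(differ by 5 or more) = 0.466 − 0.323 = 0.143.
- With an even number of men between 10 and 20, an exactly equal gender split occurs in only about 28% to 30% of runs.

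**Age.** The article gives no age distribution. Assume ages uniform over 60 to 75.

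- SD = 15 / √12 = 4.33 years.
- SE of the difference in mean age at 15:15 = 4.33 × √(2/15) = 1.58 years.
- P(mean ages differ by more than 2 years) = 2 × [1 − Φ(2 / 1.58)] = 0.21.

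**Power.** Set the standardised difference to give 85% at 15:15: d = √2 × (1.960 + 1.036) / √15 = 1.094. With arms n1 and n2, power = Φ(d / √(1/n1 + 1/n2) − 1.960).

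| Split | Power |
|---|---|
| 15:15 | 85.0% |
| 12:18 | 83.5% |
| 10:20 | 80.6% |

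**Consistency of the statements.** The odd/even rule agrees with a 1:1 ratio in expectation. It does not secure 15 per arm and does not produce matching. The matching is reported as done, while allocation is reported as pending.

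**The case against.** The best defence is that the statements can be reconciled. If the investigators form age-and-gender pairs from the enrolled list and let a random number decide which member of each pair is treated, the result is 1:1, matched and based on odd/even numbers. That also fits enrolment being complete before allocation. *Matched* may also mean only that the groups were comparable. The article condenses a fuller protocol and points to a schematic and a SPIRIT checklist that are not shown. Tenses are mixed throughout, so the timing conflict may be one of language. Finally, simple randomisation is valid: chance imbalance does not bias the comparison, and analysis of covariance is already listed.

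Much of this stands. A reader might infer that odd/even assignment cannot give 1:1, that one of the statements must be false, or that people were moved by hand. The document supports none of these. The rule is 1:1 in expectation and gives exactly 15:15 in 14% of runs, paired assignment could satisfy all three statements, and no reassignment is mentioned anywhere.

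What does not stand is that nothing needs correcting. The text attaches the number to individuals, not pairs, and two members of a pair could both draw odd. The sample-size formula is for two independent groups, and the paired t-test in Statistical analysis is for the pre/post comparison. The loose reading of *matched* is hard to hold if allocation has not happened, because there are no groups to compare. Nor is this a detail left to a fuller document: the article states a mechanism and, beside it, a property that the mechanism does not deliver.

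**Conclusion.** The concern holds in this form: the allocation description is internally inconsistent and incomplete. The stated rule gives unequal arms in 85.6% of runs, a split of 18:12 or worse in 36%, and no control of age or gender. The arm-size figures are exact for person-by-person assignment of 30 people. The gender and age figures (a gap of three or more men in 47% of runs; a mean age gap above two years in 21%) rest on assumed distributions, and they describe ordinary chance imbalance that any equal-arm scheme without stratification would share. The article does not quantify how strongly age within 60 to 75, or gender, affects the outcomes.

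Power is not the argument, since it falls by only 1.5 points at 12:18. The point is that the balance the protocol claims has no described source. Selection after numbers are drawn is a risk that the text leaves open, not something it records.

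**What to change.** 1. Reconcile Study design with Study status: say plainly whether allocation has taken place.
2. **If it has not**, freeze the list of 30 enrolled IDs and allocate all of them in one run with a recorded seed, by one of two methods:
   - Split each gender-by-age stratum in half at random and balance the odd leftovers across strata. Because 30 is even, the number of odd-sized strata is even, so leftovers can always be offset to give 15:15. Independent permuted blocks within strata would not secure this: strata of 7, 8, 7 and 8 with blocks of two leave one person over in each of two strata, and both fall in the same arm half the time, giving 16:14.
   - Form 15 age-and-gender pairs before any number is drawn, and randomise one member of each pair to intervention.

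   Replace *matched* with the method used, and include the stratification factors in the analysis of covariance already listed.
3. **If it has**, report the method actually used, delete *matched* unless a described procedure produced it, and adjust for age and gender.

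The cost is a few protocol sentences and, if allocation is still pending, under an hour of a statistician's time. No extra participants are needed.

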### Speech stimulus process

The TFS speech consists of single syllable recorded in / a / C / a / with various 16 consonant format which included Aja, Aka, Ara,…. and it is pronounced by a native-speaking man. The analogue signals are converted to digital a 16-bit at 44.1 KHz sampling frequency. The stimulus synthesis process is performed in MATLAB software and the software is provided in C programming language.

The original bandpass is filtered into 16 bands of equal bandwidth on a log frequency scale spanning 80 to 8020 Hz. Each Bandpass signal is decomposed to ENV and TFS by Hilbert transform. The ENV component is discarded and TFS component is normalized and TFS component in each band summed lastly creating TFS speech.

After rehabilitation, the SNR (50%) using the WIN test, and a binaural TFS test and SSQ questionnaire will be evaluated again in intervention group. Results will be compared in intervention and control groups before and after the rehabilitation program.

***Outcomes***.
*SNR (50%):* single syllable words in the presence of noise at different signal-to-noise ratios (0, + 4, + 8, + 12, + 16, + 20, + 24) as binaural in two study groups and compare the SNR (50%). Differences in scores before and after rehabilitation training between the two groups will be compared.

The Words-in-Noise (WIN) materials were developed to evaluate the ability of listeners to understand words in multitalker babble. The WIN involves in which the level of the noise is fixed and five words are presented at seven signal-to-noise ratios from 24 to 0 dB in 4 dB decrements. The 35 words are spoken by a native male speaker. The metric of interest is the signal-to-noise ratio (S/N) at which recognition performance is 50%, which is a value determined with the Spearman Karber equation see (
*Extended data:* S2).

Binaural TFS test: determines the binaural change of phase difference at different frequencies in intervention and control groups before and after rehabilitation training.

The correlation between the results of speech perception test scores in the presence of noise with the results of binaural TFS test in the two groups after rehabilitation program will be assessed.

*SSQ questionnaire score:* provided to each group before and after rehabilitation training. Scores between intervention and control groups will be compared (
*Extended data:* S3).

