### Study overview

We conduct a randomised clinical trial of rehabilitation training on speech in noise perception performance on an elderly population with mild to moderate hearing loss at the Audiology Clinic of School of Rehabilitation Sciences, Iran University of Medical Sciences (Tehran, Iran). It is hypothesized that the inability to use TFS speech cues is the main cause of speech perception problem in noise in elderly individuals, and it is possible by designing appropriate rehabilitation exercises to reduce the difficulty of speech perception in noise.

The Medical Ethics Committee at the Iran University of Medical Sciences approved the registered study protocol (IR.IUMS>REC.1398.003). The study was registered on the Iranian Registry of Clinical Trials (registration number,
IRCT2019625044006N1), a Primary Registry in the World Health Organization Clinical Trials Registry Network.

The protocol does not involve complications for participants in the study. All participants were informed both verbally and in writing about the study procedure. Written consent to participants were obtained from the participants before the study start (see
*Extended data:* S1).

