## Discussion

Elderly populations are growing rapidly worldwide, and this higher number of older individuals is associated with an increase in prevalence and incidence of age-related disorders. Age-related hearing loss (presbycusis) is one the most common disorders with an increase in age. Hearing loss has significant negative impact in quality of life in elderly population. It causes limitation of communication and social activity
^1^.

Speech perception in noisy environments is very serious difficulty with presbycusis, The presbycusis is known as damage of hair cells in cochlea
^5^. The hair cells damage with presbycusis mostly associated with deteriorate of temporal fine structure (TFS) information
^7^.

TFS is important when background sounds are present
^9^. Loss of speech perception in noisy environments with presbycusis is mostly caused by damage of processing of TFS information. Our study is based on improvment of TFS deficit in cochlea.

The rehabilitation training is based on identify vowel consonant vowel words (VCV). 

The test is performed in several sessions. The total time of test is three times every week for total fives week for all subjects but the time in every session is different between participants.

To evaluate the efficiency of rehabilitation training we used temporal fine structure sensitivity test (TFS test), Speech in noise test (SNR 50%) and Speech, Spatial and Qualities of Hearing Scale (SSQ) 

They are performed in both intervention and control group but at the end of study we measure only the tests in intervention population.

Initially TFS1 was developed by Moore and Sek (2009) in order to discriminate a harmonic complex tone from the same tones with all components shifted upwards by the same amount in hertz leading to an inharmonic tone. The TFS-LF was described by Moore and Hopkins (2010) to measuring thresholds for detecting changes in interaural phase difference ( IPD). Although the TFS-LF is used generally but it has a limitation. The frequency of the tones is fixed, for example at 250, 500 or 750 Hz and some old

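### The planned correlation of speech-in-noise with TFS scores uses post-programme levels only, so it cannot separate linked training gains from differences between people that existed before training

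*Protocol article*

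**What the plan says.** The Outcomes text of the protocol article (under Speech stimulus process) states one analysis that relates the two tests to each other: the correlation of speech-in-noise scores "with the results of binaural TFS test in the two groups after rehabilitation program will be assessed". The timing is therefore fixed as after the programme. Whether the two groups are analysed separately or together is not said.

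Both tests are available at baseline in everyone. Study procedures says "Pre-rehabilitation, the SNR (50%) of all participants was measured using the word in noise (WIN) test", and adds "In addition, a binaural TFS test and the SSQ questionnaire score of all participants are evaluated". For SNR(50%) itself, Outcomes already uses change: "Differences in scores before and after rehabilitation training between the two groups will be compared".

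The rationale is causal. The Study overview hypothesises that "the inability to use TFS speech cues is the main cause of speech perception problem in noise in elderly individuals", and the Discussion says "Our study is based on improvment of TFS deficit in cochlea".

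**The concern.** In a training trial, the informative question about TFS and speech in noise is whether participants whose TFS sensitivity improved more also improved more in speech perception. Post-programme levels do not address that. Someone with good TFS sensitivity and good speech-in-noise performance before training will usually have both afterwards, whatever the training did. On the protocol's own premise that poor use of TFS cues is the main cause of the difficulty, a positive correlation is expected before the first session.

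The risk is in interpretation. In a trial built on improving the TFS deficit, a significant post-programme correlation would readily be taken as support for that route of action. A weak one might be taken as evidence against it. Neither reading would be justified.

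**Working it through.** **Inputs from the protocol article.** Sample size: 15 per group, 30 in total, allowing for 20% dropout, so about 15 × 0.8 = 12 evaluable per group. Significance level: 0.05 for all tests (Statistical analysis). The article gives no figure for this correlation, so there is none to reproduce.

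**Assumed inputs (not in the documents).** Both tests are scored in the same direction with baseline SD 1.
- *r0*: correlation of the two tests at baseline.
- *rg*: correlation of the individual gains.
- *s*: gain SD divided by baseline SD, equal for both tests.
- Gains are independent of baseline.

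**Formula.** Post = baseline + gain, so the within-arm covariance is r0 + rg·s² and each variance is 1 + s²:

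r_post = (r0 + rg·s²) / (1 + s²)

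**Step 1: unrelated gains (rg = 0).** Expected post correlation:

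| r0 | s = 0.3 | s = 0.5 | s = 1.0 |
|---|---|---|---|
| 0.3 | 0.28 | 0.24 | 0.15 |
| 0.5 | 0.46 | 0.40 | 0.25 |
| 0.7 | 0.64 | 0.56 | 0.35 |

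For example, 0.5 / 1.25 = 0.40. In 20,000 simulated trials at s = 0.5, the post correlation is significant in 32% (n = 15) or 26% (n = 12) for r0 = 0.5, and in 62% or 51% for r0 = 0.7.

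**Step 2: linked gains, no baseline correlation (r0 = 0, rg = 0.8, s = 0.5).** r_post = (0.8 × 0.25) / 1.25 = 0.16, significant in 8–9% of trials at n = 12 or 15. A strong link is almost always missed.

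**Step 3: the same value from different truths.** r_post = 0.40 arises from each of these:
- r0 = 0.5, rg = 0, s = 0.5: 0.5 / 1.25.
- r0 = 0.3, rg = 0.5, s = 1: 0.8 / 2.
- r0 = 0, rg = 0.8, s = 1: 0.8 / 2.

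The observed correlation does not say which holds.

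**Step 4: if the arms were pooled without an arm term.** With a mean benefit of m baseline SDs on both tests in one of two equal arms, m²/4 is added to the covariance and to each variance. For r0 = 0.5, rg = 0, s = 0.5 and m = 1.2, r_post = (0.5 + 0.36) / (1.25 + 0.36) = 0.53. Pooled changes do not escape this: with m = 1 and rg = 0, the change correlation is 0.25 / (0.25 + 0.25) = 0.50.

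**Step 5: within-arm change correlation (s = 0.5, unadjusted).**

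| rg | significant, n = 12 | significant, n = 15 |
|---|---|---|
| 0 | 5% | 5% |
| 0.5 | 40% | 50% |
| 0.8 | 93% | 97% |

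**Step 6: precision.** By Fisher's z at n = 15, atanh(0.5) = 0.549 and 1.96/√12 = 0.566, so r = 0.5 has a 95% CI of -0.02 to 0.81. Adjusting for both baselines leaves n − 4 residual df: 11 at n = 15 and 8 at n = 12, needing |r| of about 0.55 and 0.63 for significance.

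**The case against.** A reader might infer that the protocol means this correlation to show that TFS gain explains speech gain. It does not say so. The sentence says only that the correlation will be assessed, the stated objective is the effect of training on speech in noise, and no mediation aim is given. The Study overview's causal premise concerns ability across people, and a correlation of levels is a fair descriptive companion to it. This stands: the point concerns what the result can support, not a claim the protocol has made.

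A reader might also infer that the post correlation mainly reproduces pre-existing differences. That depends on unknown inputs. The baseline share, r0/(r0 + rg·s²), with rg = 0.5 is 80% at r0 = 0.5, s = 0.5; 50% at r0 = 0.5, s = 1; 38% at r0 = 0.3, s = 1; and zero at r0 = 0. The documents do not support that wording across the range.

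Pooling is likewise only a possible reading. The reference to two groups can equally mean within each group, so the pooled 0.53 is conditional.

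The alternative has limits too. It is imprecise and remains associational, and in untrained controls change would largely reflect retest variation. The rates in Step 5 are for unadjusted changes.

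One could add that such detail belongs in a fuller plan. That would excuse silence about adjustment, but the article does fix the timing, and for a training question it fixes it badly.

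**Conclusion.** The point holds in limited form. As worded, the only analysis relating TFS to speech in noise cannot distinguish linked gains from differences present before training. Under the stated assumptions it can reach 0.15 to 0.64 when gains are unrelated, and can fall to about 0.16 when they are strongly linked. The exact size cannot be known, because the documents give neither the baseline correlation nor the spread of gains. That the two sources cannot be separated does not depend on those values.

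This is a supporting analysis, and the between-group comparison of pre-post SNR(50%) differences is not affected by it. Whether post-programme scores will exist for controls is a separate contradiction: the Discussion says "at the end of study we measure only the tests in intervention population", while Outcomes needs both groups. It adds no weight to this point, but it does bear on whether a control-arm version can be computed.

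**What to change.** Reword the sentence in Outcomes along these lines: *Within each arm, and chiefly in the intervention arm, the correlation of change in SNR(50%) with change in TFS-LF (post minus pre) will be estimated, adjusted for both baseline scores, and reported with a 95% CI as an association. Any correlation of post-programme scores is descriptive only. Arms will not be combined without a term for arm.*

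Adjusting the changes for both baselines gives the same partial correlation as adjusting the post scores for both baselines, so this amounts to adding two covariates to the planned analysis.

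The intervention-arm version uses only measurements already planned. The control-arm version first requires the statements on end-of-study testing in Speech stimulus process, Outcomes and the Discussion to be reconciled. The cost is one sentence and a wide interval: at 12 to 15 per arm the result should be read as an estimate, not a test.
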